**Methods:**

This research is designed as a two-group parallel randomized controlled trial. The total number of tooth extraction sites will be 70 after calculation with power analysis. Teeth will be randomly assigned to two groups with the test group conducting ridge preservation and the control group healing naturally. Periodontal examination, cone beam-computed tomography (CBCT) data, and stereolithographic (STL) files obtained by intraoral scanning will be collected through the follow-up period, and bone biopsy samples would be obtained during implant surgery. The primary outcomes are the vertical and horizontal change of alveolar ridge measured on CBCT images, soft tissue contour changes evaluated by superimposing the digital impressions, alterations of mucosa thickness (as measured by superimposing the CBCT data and STL files), histological features of implant sites and periodontal parameter changes. The secondary outcomes are patient-reported post-operative reaction and conditions of simultaneous bone graft or sinus lifting procedures during implantation.

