In measurement technique, most of the previous investigations usually used cone beam-computed tomography (CBCT) or peri-apical film to evaluate the change of width and height of the alveolar socket received ARP [13, 20–23]. Only a few studies reported on the three-dimensional soft tissue profile changes using intraoral scanning technique for infected molar extraction sockets [24–26].

Histological analysis is valuable in assessing and determining the clinical application of ARP, since this procedure is often related to a following dental implant therapy that requires sufficient osseointegration within genuine bone tissue [27]. Previous studies showed ridge preservation using deproteinized bovine bone mineral (DBBM) had a lower amount of new bone formation in comparison with natural healing after a follow-up period of 3–6 months [28]. Further studies with longer healing time are needed for optimizing the clinical effects of ridge preservation in periodontally compromised sockets.

Although many previous studies have confirmed the effectiveness of ARP, few studies have been conducted in periodontally compromised molar extraction sites. Soft tissues surrounding implants have significant impact on esthetics and long-term health for dental implant therapy, but the comparison between natural healing and ARP in this area is also lacking. The different histological manifestations and the effect of implant therapy for these methods are also worthy of further exploration. Therefore, this randomized controlled trial is designed to compare the efficacy of ARP and natural healing at molar extraction sites in cases with severe periodontitis. This study is expected to determine the most beneficial and least traumatic clinical treatment for such patients. The following aspects will be compared, (i) soft tissue contour and mucosa thickness change from the baseline till at least 1 year after implant loading, (ii) radiographical evaluation for vertical and horizontal change of alveolar ridge from baseline to 6 months after atraumatic tooth extraction and ARP, (iii) histological composition after 6-month healing period in /tooth extraction sites with ARP, (iv) periodontal parameter changes in the follow-up period, (v) patient-reported post-operative reaction, and (vi) finally the need of simultaneous bone graft or sinus lifting procedures during implant placement procedure.

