### Randomizing

A series of random numbers will be generated using Excel 2021 (Microsoft Corp., Redmond, WA, USA), written on letter paper and sealed in sequentially numbered, sealed, opaque envelopes. All the patients will be assigned to two groups by simple randomization with the rate of 1:1: the test group with alveolar ridge preservation, and the control group with natural healing. All the surgical procedures will be performed by an experienced clinician, and the other clinician will conduct the clinical examination for the patients. Another two members will take charge of intraoral scanning, assessing the radiological examinations and completing statistical analysis.

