### Blinding

Blinding is not suitable for this trial. For the participants, they can distinguish which group they are in after experiencing different surgical procedures and post-operative treatment, so can the surgeons. For the assessors, they can also differentiate two groups from different imaging manifestations.

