**Fig. 3 Fig3:**
[figure not shown]
Flowchart of data collection during follow-up period

At baseline (before tooth extraction), the following data will be collected:Full-mouth peri-apical films,CBCT images (CBCT 1): CBCT images will be taken by CBCT machines (NewTom VG; Aperio Services, Italy) at a resolution of 0.125 mm with field of view size 10 × 10 cm (exposure time: 3.6 s, 110 kV, 5 mA). It will be used for assessing anatomical conditions, including the degree of bone loss and the position of maxillary sinus/mandibular canal.Stereolithography (STL) files (STL 1): intraoral scans will be taken using a TRIOS intraoral scanner (3Shape TRIOS Color, TRC, 3Shape, Denmark) to obtain a digital impression of the target area and generate an STL file, which include the selected tooth and relevant quadrant. Soft tissues contained in this digital impression will extend over the mucogingival junction.Periodontal parameters: the periodontal conditions of the ailing tooth and adjacent teeth will be assessed by measuring probing depth (PD), gingival recession (GR) and bleeding index (BI). The width of keratinized tissue (WKT) will be measured at mid-buccal aspect from the mucogingival junction to the gingival margin of the teeth. Data will be round down to the nearest 0.5 mm, and they will be collected using an UNC-15 probe (Hu-Friedy, Chicago, IL, USA).

#### 
Examination immediately after the intervention for both groups (Fig. 3)

CBCT images (CBCT 2): it will be used for superimposition and measurement. And it will be illustrated in informed consent.STL files (STL 2)

#### 
Examinations during the follow-ups before implant therapy (Fig. 3)

STL files (STL 3–6): the patients will be recalled at 2, 4, 12 weeks and 6 months after the surgery, and intraoral scans will be performed.CBCT images (CBCT 3): CBCT examination will be performed 6 months after the surgery.Post-operative reaction: the patients will be recalled at 1, 2 and 4 weeks after the surgery to report post-operative reaction, such as pain, erythema, swelling and paranesthesia.Paralleling technique films: films will be taken 6 months after the surgery.Periodontal parameters: at 6 months after the surgery, the periodontal examination indicators (PD, GR, BI and WKT) will be recorded for the adjacent teeth, and WKT of extraction area will also be measured at the buccal aspect from the central of the (expected) implant position to the buccal mucogingival junction [32].

#### 

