Examination during implant therapy (Fig. 3)

The implant therapy will be performed around 6 months after ARP/tooth extraction.Bone biopsy: during the implant placement procedure, a cylindrical bone block with a diameter of about 2 mm and length of about 5 mm will be taken out using a trephine drill (Institute Straumann AG, Basel, Switzerland). The block will be fixated in 4% formaldehyde solution at room temperature for at least one day. Then, they will receive decalcification for 3 weeks in 4.1% disodium ethylene-diamino-tetra-acetic acid-solution, the solution will be changed every 24 h. After hydration, they will be dehydrated in increasing concentrations of ethanol (from 70 to 100%), embedded in paraffin, and cut into sections with a thickness of 4 µm. Serial sagittal sections will be stained with hematoxylin–eosin. Representative regions of interest (ROIs) will be localized in the center, apically and coronally of the sample [33]. Histologic slides will be observed under light microscopes and digital images will be obtained by scanning at a magnification of × 200 for subsequent histomorphometric analysis. For the two groups, the histological composition in terms of new bone formation, residual graft particles and connective tissue will be evaluated and compared.Simultaneous bone graft & sinus lifting procedures: the conditions of bone grafting and sinus lifting during implant therapy will be recorded.

#### 
Examination during the follow-ups after implant restoration (Fig. 3)

After 6-month period of osseointegration, the superstructures will be connected to the implants. Participants will be recalled at immediately, 1-, 3-, and 6-month and then every 6 months after implant loading. During this period, the following data will be collected:STL files (STL R1, R2, and so on): intraoral scans will be performed at every appointment.Periodontal parameters: the periodontal examination indicators (PD, GR, BI and WKT) will be recorded for the implant and adjacent teeth at every appointment.Paralleling technique films: the films will be collected immediately and every 6 months after implant loading, and they will be used to evaluate the marginal bone loss (MBL).

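### The secondary outcome described as the need for bone graft or sinus lift is obtained only as procedures performed, chosen by an operator who knows the arm

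*Protocol article*

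**What the plan says.** The last paragraph of the Background lists the aspects to be compared. The sixth is "the need of simultaneous bone graft or sinus lifting procedures during implant placement procedure". The Abstract ranks the item as secondary and words it differently: "The secondary outcomes are patient-reported post-operative reaction and conditions of simultaneous bone graft or sinus lifting procedures during implantation". Under Methods, the subsection on the examination during implant therapy gives the only description of how the outcome is obtained: "the conditions of bone grafting and sinus lifting during implant therapy will be recorded".

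On who operates, the Randomizing section says "All the surgical procedures will be performed by an experienced clinician". It gives clinical examination to a second clinician, and scanning, radiological assessment and statistics to two further members. On masking, the Blinding section says "Blinding is not suitable for this trial". It explains that participants can tell their group from the procedures they undergo, adds "so can the surgeons", and says the same of assessors because the images look different.

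A scan is already planned before implant surgery: "CBCT examination will be performed 6 months after the surgery" (CBCT 3). It is used for changes in width and height relative to CBCT 2. The article does not link it to the augmentation outcome.

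**The concern.** Need and procedure performed are different quantities. Need is a property of the ridge at the time of implant placement. A procedure performed is a treatment decision, and in borderline sites it leaves room for judgement. If the person deciding knows the arm, two sites with the same bone can be handled differently, and that difference enters the data as an outcome.

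The expected direction is on record. Both the Background and the Discussion cite earlier work in which ridge preservation reduced the necessity of augmentation at implant placement. If controls are grafted more often, the trial as written cannot separate a real effect on bone from a lower threshold for grafting in sites known to be unpreserved. This outcome would be used to say that ridge preservation spares a later procedure, which bears on the stated aim of finding the most beneficial and least traumatic treatment.

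**Working it through.** **Step 1: the text side by side.**

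| Question | Where | Answer |
|---|---|---|
| What is compared? | Background, aim (vi) | Need for augmentation |
| What is collected? | Examination during implant therapy | Grafting and sinus lifting as carried out |
| Who decides? | Randomizing | One clinician for all surgery; implant placement is not named separately |
| Does the decider know the arm? | Blinding | Yes |
| What rank? | Abstract | Secondary |

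The first two rows name different quantities. The third and fourth make the collected quantity an open-label decision.

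**Step 2: the number of sites.** The Sample size calculation gives 30 per group. With means 1.46 and -0.70 mm and SDs 3.54 and 2.28 mm, n = (1.960 + 0.842)² × (3.54² + 2.28²) / 2.16² = 7.85 × 17.73 / 4.67 = 29.8, so 30. The plan's figure reproduces. It was sized on ridge width, and it is used here only as the number of evaluable sites per arm.

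**Step 3: an illustration under assumption.** The documents give no augmentation rate and no information on any arm-driven shift, so both are assumed. Let the true need be p = 0.40 in both arms. Let the procedure be done with probability p in the ridge preservation arm and p + s in the control arm, where s comes only from knowledge of the arm. The rejection probability is the sum, over all pairs (a, c) from 0 to 30, of Bin(a; 30, p) × Bin(c; 30, p + s) for those pairs with a two-sided p-value of at most 0.05.

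| s (points) | Sites in 30 | Chi-square rejects | Fisher rejects |
|---|---|---|---|
| 0 | 0 | 4.9% | 2.6% |
| 10 | 3 | 12.3% | 7.7% |
| 15 | 4.5 | 21.8% | 14.8% |
| 20 | 6 | 35.0% | 25.7% |

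The chi-square test is uncorrected. At s = 20 points, 34.9 of the 35.0 percentage points are rejections in favour of ridge preservation.

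**Step 4: sensitivity.** With a true need of 30% or 50% and 30 sites per arm, the chi-square figures stay at 12%, 22% and 35%. With 35 sites per arm and a true need of 30% to 50%, they are 12% to 14%, 22% to 25% and 36% to 40%. The result depends on s, which the documents cannot supply, and hardly at all on the assumed need.

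**The case against.** Several points against this carry weight.

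- **Same surgeon.** A reader might infer that the person who placed or withheld the graft is certain to judge the result six months later. The documents do not establish this. The article does not name who places the implants, the sentence on all surgical procedures can be read as covering that step without saying so, and the Blinding section speaks of surgeons in the plural. The narrower statement stands: whoever operates is not masked.
- **Rank.** The outcome is secondary and the sample size rests on ridge width. The CBCT ridge outcomes are not affected by this route.
- **Existing check.** Width and height changes from CBCT 2 to CBCT 3 are planned, and radiological assessment is assigned to members other than the surgeon. A difference in augmentation with no matching difference in bone would be visible. This helps interpretation, but change from CBCT 2 is not available bone at an implant position, and it is not tied to this outcome.
- **Condensed article.** The full protocol may hold a definition of need or written indications. That is why the absence of a criterion alone is not the point. The point is that the article names one quantity, collects another, and states that the person choosing it knows the arm.
- **Legitimate endpoint.** Procedures actually undergone matter to patients and deserve reporting. This supports keeping them under their own name; it does not make them a measure of need.
- **Assumed shift.** The table in the working takes the shift as an input. It shows what a bias of a given size would do and is not evidence that such a bias will occur.

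**Conclusion.** The point holds as an improvement to a secondary outcome. As described, the comparison of need rests on procedures chosen with knowledge of the arm, so expectation can contribute to any difference found. It cannot be said that the outcome is biased: citing earlier favourable studies shows a known expected direction and does not show that decisions will be distorted. A real effect of ridge preservation on bone could equally reduce augmentation.

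The size cannot be computed from the documents. The figures of 12%, 22% and 35% against 5% rest on 30 evaluable sites per arm, an equal true need of 40%, an uncorrected chi-square test, and assumed shifts of 10, 15 and 20 points. They should be read as conditional illustrations. They are not estimates of this trial's false-positive rate.

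**What to change.** Amend aim (vi) in the Background and the subsection on the examination during implant therapy in two ways.

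1. Report grafting and sinus lifting under the name procedures performed, as a separate outcome.
2. Add a need outcome scored on CBCT 3 for every randomised site that has that scan. The existing CBCT assessors, not the surgeon, measure ridge width and available height at an implant position set by a written rule. They score these against a numerical criterion that the investigators fix in writing before any CBCT 3 is read. Compare the arms on this score.

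The surgeon's clinical decision stays free, and no threshold is proposed here.

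The cost is a short amendment plus one planning and measurement step per scan, on images already scheduled. The gain is limited: the Blinding section says assessors can also tell the groups apart on imaging, so readers may recognise grafted sites. A measurement-based criterion narrows the room for judgement and reduces the bias, but does not remove it.

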#### Superimposition and measurement of CBCT images and digital impressions

CBCT images: Digital Imaging and Communications in Medicine (DICOM) data will be generated and transferred to a volumetric imaging software (Mimics 21.0, Materialise, Leuven, Belgium). Residual buccal and lingual (or palatal) plate thicknesses and height of residual socket walls can be measured and recorded with vertical/horizontal reference lines and dots on CBCT 2. After Superimposition of CBCT 2 and CBCT 3, horizontal width and vertical height changes at target sites will be calculated; details are discussed in the previous literature [13, 17].STL files: these data will be generated and imported to Geomagic Studio 2021 (3D Systems Inc., Rock Hill, SC, USA). Superimposition of STL 1 and STL files for subsequent stages (STL 2–6, STL R1, and so on) will be completed for the selected areas, using identified landmarks such as cusps of adjacent teeth. After superimposition, the impressions can be aligned and manually checked for perfect matching, and changes of the contour lines of alveolar ridge can be observed and measured.CBCT data and STL files: As described in previous literature [25], CBCT 2 and STL 3 will be superimposed in Geomagic Studio 2021 (3D Systems Inc., Rock Hill, SC, USA) using three or more landmarks of adjacent teeth and so will CBCT 3 and STL 6. The vertical thickness of the crestal mucosa and horizontal thickness of the buccal and palatal/lingual mucosa and their alterations will be measured.

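### Two soft tissue outcomes cannot be analysed as stated: mucosa thickness has no CBCT after 6 months for its 1-year objective, and extraction-site keratinized tissue width changes landmark between baseline and 6 months

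*Protocol article*

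**What the plan says.** The Abstract lists several primary outcomes. Two matter here: "alterations of mucosa thickness (as measured by superimposing the CBCT data and STL files" and "histological features of implant sites and periodontal parameter changes"; the periodontal parameters include WKT. The last paragraph of the Background gives the time window for the first: "soft tissue contour and mucosa thickness change from the baseline till at least 1 year after implant loading".

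Under Outcome measures, CBCT 2 and STL 2 fall under "Examination immediately after the intervention for both groups". For STL 3 to 6, "the patients will be recalled at 2, 4, 12 weeks and 6 months after the surgery, and intraoral scans will be performed". CBCT 3 is taken at 6 months. After restoration the listed data are scans, periodontal parameters and paralleling films for marginal bone loss.

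The section on superimposition describes two combinations of CBCT and scan for mucosa thickness: "CBCT 2 and STL 3 will be superimposed in Geomagic Studio 2021", and CBCT 3 with STL 6.

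At baseline, WKT "will be measured at mid-buccal aspect from the mucogingival junction to the gingival margin of the teeth". At 6 months, WKT of the extraction area runs "from the central of the (expected) implant position to the buccal mucogingival junction". After loading it is recorded for the implant, with no landmark given.

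The Statistical analysis section plans a paired t-test or signed rank test for soft and hard tissue change between the time before surgery and 6 months after it, and a t-test or Mann–Whitney test between arms.

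**The concern.** A change outcome needs the same quantity measured at both ends of its window. Mucosa thickness fails at both ends: nothing in the listed schedule yields a value 1 year after loading, and the first value is not from before surgery. Extraction-site WKT fails because its coronal landmark moves when the tooth is removed.

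If left as written, one stated objective cannot be answered from the data collected. One within-group test would report a shift that is partly a change of definition, and a reader could take it as a gain in keratinized tissue in both arms.

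**Working it through.** No planned figure attaches to either outcome. The sample size rests on CBCT ridge width and is not touched by this point. The check is a time map and a comparison of definitions.

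**Mucosa thickness.** Four scans (STL 3 to 6) are matched in order to four recall times, so STL 3 is the 2-week scan and STL 6 the 6-month scan.

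| Thickness value | Bone surface | Mucosal surface |
|---|---|---|
| First | CBCT 2, day 0 | STL 3, 2 weeks |
| Second | CBCT 3, 6 months | STL 6, 6 months |
| After loading | none listed | STL R1 onwards |

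- Loading: about 6 months to implant placement + 6 months of osseointegration = month 12.
- Earliest end of the objective's window: 12 + 12 = month 24.
- Last CBCT: month 6. Stretch without a bone surface: 24 − 6 = 18 months, or 18/24 = 75% of the window.
- Combining CBCT 3 with later scans is not planned. It would also be doubtful, because implant placement, with grafting or sinus lifting at some sites, follows CBCT 3 and can alter the bone surface.
- CBCT 1 and STL 1 are the only pre-extraction pair, and they are not superimposed for thickness. Neither thickness value is therefore from before surgery.

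**Extraction-site WKT.** Let M be the distance from the buccal edge of the crest (the gingival margin, while the tooth is present) to the mucogingival junction. Let h be the distance from the centre of the expected implant position to that buccal edge.

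- Baseline value = M0.
- 6-month value = M6 + h.
- Apparent change = (M6 − M0) + h.

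A paired test of zero change therefore tests (M6 − M0) + h, and h is positive even when the tissue has not changed. If the implant centre lies mid-crest, h = w/2 for crest width w. The documents give no crest width. On an assumed range of 6 to 10 mm, h = 6/2 to 10/2 = 3 to 5 mm.

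Between arms at 6 months, the same definition applies on both sides. The difference is (difference in M6) + (difference in w)/2, so each 1 mm of extra ridge width in one arm contributes about 0.5 mm. As an illustration, the ridge width difference used for the sample size is 1.46 − (−0.70) = 2.16 mm. If it appeared in full at the crest, it would contribute 2.16/2 = 1.08 mm. That figure was for one CBCT site 1 mm below the crest, so this shows only the order of size.

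**The case against.** On thickness, the 1-year window appears in one compound phrase that also covers contour, and contour does run to 1 year. The Abstract sets no time for thickness, and the operative method stops at 6 months. This may be loose wording, and the schedule figures are not available in the text reviewed. That lowers the weight of the point but does not remove it: the objective as worded names thickness, and no text provides a later CBCT.

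On WKT, a new landmark is unavoidable once the tooth is gone, and the 6-month definition is given openly with a citation. The paired test is worded generically and does not name WKT. These points stand. Even so, periodontal parameter changes are a primary outcome, WKT is measured at both times, and nothing exempts the extraction site from the test.

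Four stronger readings are tempting, and the documents do not support them:

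- *All primary soft tissue changes are compromised.* Contour is superimposed on a single reference, STL 1, throughout. Probing depth, recession, bleeding index and adjacent-tooth WKT have no stated change of definition.
- *Pairing CBCT 2 with STL 3 biases the arm comparison.* The flap and coverage do differ by arm, but the pairing follows a cited method and has a plausible reason. On day 0 the test socket is covered by collagen sponge and suture, which a same-day scan would record, and sutures come out at 2 weeks. No size or direction of bias can be derived. Replacing the pair with CBCT 1 and STL 1 is debatable, because crestal mucosa over the socket does not exist while the tooth is in place.
- *The 6-month WKT comparison between arms is invalid.* It uses one definition in both arms. Its dependence on ridge width is a matter of interpretation.
- *WKT change could be rescued by comparing tooth margin with implant margin after loading.* The plan gives no implant landmark, implant surgery intervenes, and only sites that reach loading would contribute.

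**Conclusion.** The point holds for two outcomes and no further. The mucosa thickness objective cannot be met as worded: about 18 of about 24 months have no planned thickness value, and the starting value is an early post-operative one. This rests on the CBCTs listed in the text being complete.

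The before-versus-6-month paired test for extraction-site WKT would mislead as written. The direction of the artefact, towards an apparent gain, follows from the two definitions wherever the implant centre lies lingual to the former margin. Its size, about 3 to 5 mm, rests on an assumed 6 to 10 mm crest with the implant centred on it. The randomised comparison of contour and the other periodontal parameters is not called into question.

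**What to change.** 1. Restrict the mucosa thickness objective to 6 months after surgery, and keep the window to at least 1 year after loading for scan-based contour only.
2. Describe the first thickness value as an early post-operative reference (day-0 bone surface, 2-week mucosal surface), and do not label it baseline or pre-surgical in the objective or the analysis section.
3. Drop the paired test for extraction-site WKT. Compare the 6-month value between arms with baseline WKT as covariate; a covariate need not share the outcome's definition. State that the 6-month measure partly depends on ridge width.
4. Keep the change analyses for adjacent teeth.

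The cost is a narrower objective and one lost within-group test. The changes are to wording and analysis only, with no new imaging or visits.

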### Intervention

The enrolled patients will receive clinical and radiological examinations. They will receive routine scaling and root planing, and oral hygiene instruction at least 1 week before the surgery. All the patients will also receive prophylactic antibiotic medicine (Amoxicillin, 1 g or Erythromycin 300 mg if allergic to Penicillin) and anti-inflammatory drug (Ibuprofen 300 mg) 1 h prior to the surgical procedures described previously [31].

For control group:An internal bevel incision will be performed from 0.5–1.0 mm below the buccal and lingual gingival margin to the bone crest.The selected tooth will be extracted atraumatically [31].The socket will be examined carefully and debrided thoroughly (using P24G Periosteal Elevator and CL86 Lucas Surgical Curette) without damaging the socket walls.

For test group:The steps mentioned above are the same.A full thickness flap will be elevated to expose 2 mm of the bone crest.The socket will be filled with DBBM (Bio-Oss, Geistlich Pharma AG, Wolhusen, Switzerland), and a resorbable membrane (Bio-Gide, Geistlich Pharma AG, Wolhusen, Switzerland) will be used to cover the socket completely with 2 mm extending over the crest.Then the socket will be covered by collagen sponge (Wuxi Biot Biology Technology Co.,Ltd., Wuxi, China).A cross-mattress tension-free 5–0 suture will be placed over the site.

After the surgical procedures, patients will be prescribed to take the antibiotic three times daily for 7 days and ibuprofen (300 mg twice daily for 3–5 days) if needed. Patients will be required to perform regular tooth brushing in the rest of the mouth and oral rinse with 0.12% chlorhexidine solution for the 4-week post-surgery. The sutures will be removed 2 weeks after the surgery, and all the patients will be recalled at 4 weeks after the surgical to evaluate the healing status of the surgery site.

During the whole follow-up period from baseline to the last appointment, all the participants will receive regular maintenance therapy.

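### The starting crestal mucosa thickness takes its bone surface from a scan made after treatment, so its change to 6 months can be confounded with socket fill

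*Protocol article*

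**What the plan says.** The Abstract (Methods) of the protocol article lists among the primary outcomes "alterations of mucosa thickness (as measured by superimposing the CBCT data and STL files".

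The section on superimposition and measurement fixes the scan pairs, the same for both arms. For the start, "CBCT 2 and STL 3 will be superimposed in Geomagic Studio 2021"; for 6 months, the match is made "using three or more landmarks of adjacent teeth and so will CBCT 3 and STL 6". From these pairs, "The vertical thickness of the crestal mucosa and horizontal thickness of the buccal and palatal/lingual mucosa and their alterations will be measured". No landmark or bone-surface rule for mucosa is printed. The method is referred to a cited study (reference 25).

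Under Outcome measures, CBCT 2 stands below the heading "Examination immediately after the intervention for both groups", with its purpose given as "CBCT images (CBCT 2): it will be used for superimposition and measurement". By the follow-up schedule, STL 3 is the 2-week scan, and STL 6 and CBCT 3 are taken at 6 months.

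Under Intervention, the last control step listed is "The socket will be examined carefully and debrided thoroughly", without damage to the walls and with no filler. The test arm continues: "The socket will be filled with DBBM (Bio-Oss, Geistlich Pharma AG, Wolhusen, Switzerland), and a resorbable membrane" then covers the socket.

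Outcome measures defines baseline as before extraction, and the first objective in the Background is mucosa thickness change from baseline. Statistical analysis plans paired tests within arms from before surgery to 6 months, and independent-samples t or Mann–Whitney tests between arms.

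**The concern.** A change score is a fair between-arm comparison when its starting value is measured before treatment or is otherwise untouched by it. Here the hard-tissue surface that sets the starting thickness is recorded after treatment, and treatment alters that surface: in one arm the socket holds graft, in the other it is unfilled.

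The vertical crestal reading is the most exposed. If it is taken over the socket opening, the test-arm distance stops at the graft, while the control distance runs on into the empty socket. By CBCT 3 the control socket has healed, and the bone that filled it appears as a loss of mucosa thickness. The controls would seem to thin and the test arm would not, even if the mucosa behaved identically. The control-arm paired test would carry the same artefact. Since the outcome is primary, a false soft-tissue conclusion is at stake.

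Changing the soft-tissue scan paired with CBCT 2, for example to STL 2, would not help, because the difficulty lies in the bone reference.

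**Working it through.** **1. The plan's own figure.** The only sample size calculation concerns ridge width change: means 1.46 and −0.70 mm, SDs 3.54 and 2.28 mm, two-sided alpha 0.05, power 0.8.

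n per arm = (SD₁² + SD₂²)(z₀.₉₇₅ + z₀.₈)² / δ² = (12.53 + 5.20) × 7.85 / 2.16² = 29.83, so 30.

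The stated 30 reproduces. The article has no figure for mucosa thickness, so 30 is used below only as the planned number of evaluable sites per arm.

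**2. What each reading rests on.**

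| Reading | Bone surface | Test socket then | Control socket then | Soft-tissue surface |
|---|---|---|---|---|
| Start | CBCT 2, just after surgery | graft under membrane | debrided, unfilled | STL 3, 2 weeks |
| End | CBCT 3, 6 months | healed | healed | STL 6, 6 months |

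The start row differs by arm because of the treatment itself. The end row has no open socket in either arm.

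**3. The offset, if the reading is taken over the opening.** Let d be the unfilled control depth, s_C and s_T the heights of the scanned tissue above crest level at the first scan (control, test), and t₆ the 6-month thickness, taken as equal in both arms. Assume the graft reaches crest level.

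- Control change = t₆ − (d + s_C)
- Test change = t₆ − s_T
- False difference D (test minus control) = d + s_C − s_T

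The only socket dimension in the article is the 3 mm wall criterion under Participants. Treating it as d is an assumption. With d = 3 mm, D is 3 mm if the tissue surfaces are level, 1 mm if the control surface is 2 mm lower, and 0 if it is 3 mm lower. If the landmarks exclude the void altogether, D is also 0.

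**4. Effect on the planned test.** Welch t test, 30 per arm, two-sided 0.05, no true difference in mucosal change. The rejection probability comes from the noncentral t distribution with noncentrality D / √(SD_T²/30 + SD_C²/30). Two examples for D = 1 mm:

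- SDs 1 and 1: standard error √(2/30) = 0.258, noncentrality 3.87, rejection 97%.
- SDs 3.54 and 2.28: standard error √(17.73/30) = 0.769, noncentrality 1.30, rejection 25%.

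| D (mm) | SD of change, test/control 1/1 | 1/2 | 1/3 | 3.54/2.28 |
|---|---|---|---|---|
| 0 | 5% | 5% | 5% | 5% |
| 0.5 | 48% | 22% | 13% | 10% |
| 1 | 97% | 67% | 39% | 25% |
| 2 | 100% | 99.8% | 92% | 72% |
| 3 | 100% | 100% | 99.9% | 97% |

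Every D is assumed. The first three SD pairs are assumed, and the last is borrowed from the ridge width calculation. None is a mucosa figure from the article.

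**The case against.** The strongest reply is that the article prints no rule sending the vertical reading to the socket floor. It names scan pairs and quantities and leaves the method to a cited study. The Discussion describes that study as a comparison of ridge preservation with spontaneous healing using intraoral scans and CBCT over 6 months, so its method has been used in unfilled sockets. The measurement section also places reference lines and dots on CBCT 2 for the residual walls. A reading at the wall crests, or from a line joining them, would not equal socket depth. Landmark detail is something a condensed article may leave to the full protocol.

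Most of this stands. A reader might infer that the control starting value simply is socket depth, or that a significant result is bound to follow whatever the mucosa does. The documents support neither: the first needs a landmark rule that is not printed, and the second needs an offset that may be small or zero. A reader might also extend the point to all buccal and palatal/lingual readings. That could apply only at levels where the wall is lost, and it is not shown.

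The reply does not remove the printed facts on timing. CBCT 2 follows treatment, the sockets differ by arm at that moment, and a change from that point is the outcome. A line joining the crests would still start controls from a constructed surface over an open socket and end them on real bone.

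**Conclusion.** The point holds in conditional form and is worth acting on. What the article establishes is that the starting crestal thickness depends on a post-treatment bone surface that differs by arm, so it is neither a common baseline nor the pre-extraction baseline named elsewhere in the article. What remains conditional is the bias: if the vertical reading is taken over the opening, the control change includes socket fill and the between-arm difference in change is confounded with it.

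The size cannot be derived from the documents. At 30 sites per arm and under the assumed SDs, false rejection runs from the nominal 5% with no offset, through 25–97% at 1 mm, to about 97% or more at 3 mm. The 6-month value does not share the problem.

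**What to change.** - Make the between-arm comparison of crestal mucosa thickness on the 6-month value (CBCT 3 with STL 6).
- Do not test the CBCT 2-based crestal change, either between arms or within controls, as a mucosal effect.
- If a crestal change is still reported, keep it descriptive, with a bone reference fixed on native wall crests and identical in both arms.
- Keep change scores for buccal and palatal/lingual thickness where a native wall is present on CBCT 2.
- Align the wording of the primary outcome in the Abstract, the first objective in the Background, and the measurement section.

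The cost is wording only, with no new images, visits or patients. The small loss is that crestal mucosa has no inferential change-from-start result, although change is what the primary outcome now names.
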